#### Cost analysis of the mental health service strengthening model.

The objective of the cost analysis is to assess the incremental costs associated with the intervention package from both the provider’s and patient’s perspectives. This will involve determining the costs related to the development, implementation, and scale-up of the intervention package, which aims to integrate the screening, detection, and management of selected MSUDs with NCD care.

The cost analysis aims to determine both financial and economic costs of the mental health service strengthening model. The focus of financial cost analysis will be on identifying and costing the additional resources required for the development and implementation of the intervention package. These estimates will offer essential inputs to inform budgetary planning and resource allocation decisions. In contrast, the economic cost analysis will involve identifying and valuing all resources used in the development and implementation of the intervention, regardless of whether they involve direct financial outlays. This includes existing resources such as infrastructure, personnel time, and donated goods or services, thus capturing the full opportunity cost of the intervention [36]. Cost analysis using an economic standpoint is intended to inform any future economic evaluation, such as cost-effectiveness analysis, should such an assessment be undertaken subsequently.

#### Conceptual framework for costing of intervention package.

A stepwise approach will be followed to assess the cost of the intervention package in each district from a healthcare perspective. The activities in the intervention package will be identified as either new activities (initiated as part of the intervention package) or old activities (any existing activities likely to be affected in scale due to the intervention). Subsequently, the new activities (such as digital platforms, etc.) will be costed in three phases during the implementation of the refined model in one block (henceforth referred to as the Mref block). The information on resources used and the associated costs will be acquired through a top-down micro-costing methodology in a retrospective as well as prospective manner. The data related to the start-up costs will be obtained at the beginning of the implementation of the refined model. Since the intervention is likely to require time for uptake (3 months), therefore, a similar data collection on resources and costs related to the intervention package will be conducted at the end of the third month of implementation (early implementation costs) and in the 12^th^ month to estimate the late implementation costs. The outputs related to the intervention will also be determined at the three timepoints. This process will help estimate the total cost of implementing the intervention in its first year, with late implementation costs aiding in the estimation of the ongoing costs to sustain the intervention model.

Additionally, the activities identified as ‘old activities’ will be costed at two cross-sectional timepoints (baseline and endline). The baseline costs will reflect the cost of activity without implementation of the intervention package. Therefore, this data collection will be conducted in a non-intervention block (future Mref block) during the implementation of the first test model (M0). Information regarding inputs as well as outputs will be acquired along with the related costs in order to determine the per-unit cost of activity (without the intervention package in place). Since these activities are already established, it is assumed that they will experience an immediate scale-up once the Mref model is implemented. Therefore, we plan to collect the data on inputs and outputs only in the last month of the implementation of Mref. The cost difference between the baseline and endline data will reflect the incremental cost associated with increasing the intensity and coverage of services. Combining the costs of new activities with the incremental cost of old activities at the achieved coverage level will enable the calculation of the unit cost for the mental health service strengthening model.

Finally, using the patient’s perspective, the out-of-pocket expenditure to access mental health care services (screening/ management) will be determined at a single time-point across different levels of care (Fig 4).

**Fig 4 pone.0332359.g004:**
[figure not shown]
Conceptual framework for costing of intervention package.

### Data Collection

A top-down micro-costing method will be employed. Simple random sampling will be used to select primary [2], secondary [1], and tertiary care facilities [1] per district for data collection on the costing of all the components of the intervention package. In total, 28 facilities will be surveyed to gather data on the inputs and outputs associated with the components of the intervention package.

A semi-structured data collection instrument will be developed, tailored to the components of the refined intervention package. This tool will enable the collection of information on the number and types of services provided for the selected mental health disorders, as well as the value of input resources, including personnel, building space, equipment, furniture, medicines, consumables, and utilities. A structured time allocation tool will also be developed to capture the time spent on various activities by each staff member involved in the delivery of mental health services during the reference year. Data will be gathered through face-to-face interviews with healthcare personnel engaged in different activities, non-participant observations during service delivery, and a review of relevant records.

The details of out-of-pocket expenditure will be obtained through exit interviews at randomly selected primary, secondary, and tertiary care facilities in each district. A total of 200 patients and 20 patients of selected MSUDs visiting outpatient department and inpatient department respectively in the secondary and tertiary care facilities, and 120 individuals visiting the primary healthcare facilities for seeking care for these disorders will be recruited in a consecutive manner. After acquiring an informed written consent, face-to-face interviews will be conducted using a semi-structured instrument, comprising of socio-demographic details, clinical characteristics, and out-of-pocket expenditure. Details on components of both direct medical and non-medical expenditure will be elicited from the participants. Direct medical expenditure will include expenses incurred on the user fee, diagnostic tests, drugs, consumables etc. The direct non-medical expenditure will include expenses on transportation, accommodation, and food for the patient as well as their acquaintances, spent for accessing the mental health services [37].

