### Aims & objectives

The aims of the study are to develop, assess the feasibility, implement a service delivery model to achieve high coverage (≥70%) of screening, management, and linkage to care of common mental disorders (CMDs) and substance use disorders (SUDs) among individuals seeking care for non-communicable diseases (NCDs) at public health facilities and to evaluate the cost associated with the implementation of the proposed service delivery model.

The primary objective is to develop and implement a service delivery model that would result in high coverage (at least 70%) of screening, management, and linkage to care of common MSUDs among persons seeking care for NCDs at public health facilities. The secondary objectives are to (a) assess the feasibility of adoption of the implementation model by the health care system and (b) evaluate the costs of the mental health service strengthening intervention package from the health system as well as the patient’s perspective.

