### Study population

The target population includes individuals aged 18 years and above who seek care for NCDs. The study population shall be the healthcare workers of all cadres across healthcare facilities at various levels of healthcare delivery (including Ayushman Arogya Mandirs, sub-centers, PHCs, CHCs, district hospitals, and tertiary care hospitals)

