### Data analysis

The data on the quantity and associated costs of input resources will be recorded in Microsoft Excel. The costs of shared resources, such as human resources, space, equipment, and furniture, will be allocated to specific services using appropriate apportioning methods. The total and per-unit incremental costs incurred, along with their distribution across the various types of inputs and services provided at each facility, will be determined. Additionally, the mean out-of-pocket expenditure per individual will be calculated based on the type of service accessed (screening or management of selected disorders).

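### The out-of-pocket cost of screening is promised as a separate mean, but the exit-interview recruitment rule leaves out NCD attenders who are screened and found negative

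*Protocol article*

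**What the plan says.** Secondary objective (b), under Aims & objectives, is to cost the intervention package from the health-system and the patient perspective. For the patient side, the section Conceptual framework for costing of intervention package states that "out-of-pocket expenditure to access mental health care services (screening/ management) will be determined at a single time-point across different levels of care". The Data analysis section of the cost work makes screening a reported quantity of its own: "the mean out-of-pocket expenditure per individual will be calculated based on the type of service accessed (screening or management of selected disorders").

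The respondents are defined once, under Data Collection. At the higher levels they are "200 patients and 20 patients of selected MSUDs visiting outpatient department and inpatient department respectively in the secondary and tertiary care facilities". At the primary level, "120 individuals visiting the primary healthcare facilities for seeking care for these disorders will be recruited in a consecutive manner".

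The people the model serves are defined differently. Under Study population, "The target population includes individuals aged 18 years and above who seek care for NCDs". The primary objective concerns "screening, management, and linkage to care of common MSUDs among persons seeking care for NCDs at public health facilities", and the first primary outcome takes NCD care-seekers as the denominator for screening.

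**The concern.** The quantity promised and the people interviewed do not match. In this model nobody has to be looking for mental health care to be screened: a person comes for diabetes or hypertension, say, and is screened at that contact. The interview rule instead selects on having an MSUD or coming for one. That removes the people whose screening ended with a negative result, and their spending belongs in any mean cost of being screened.

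A second, softer problem concerns management. The package being costed joins MSUD services to NCD care, but the interview rule asks neither for an NCD nor for entry through the model. A consecutive series of MSUD outpatients and inpatients could include people whose visits the model did not generate.

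At stake is the patient-perspective part of secondary objective (b). The screening mean would be read as what the package costs a screened NCD patient, and the management mean as what it costs a patient managed through the model. Neither reading is secured by the recruitment rule. No primary outcome is affected.

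**Working it through.** **Counts in the plan.** Facilities for the costing survey: (2 primary + 1 secondary + 1 tertiary) × 7 districts = 28, which agrees with the stated figure. Exit interviews: 200 + 20 + 120 = 340. The article gives no formula or precision target for these counts, so there is nothing to re-derive. It is also not clear whether 340 is the study total or a per-district number (340 × 7 = 2,380). The point does not depend on which.

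**Who can be interviewed, group by group.**

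| Group | Number | Stated condition | NCD attender, screened, negative |
|---|---|---|---|
| Secondary/tertiary outpatients | 200 | has a selected MSUD | not eligible |
| Secondary/tertiary inpatients | 20 | has a selected MSUD | not eligible |
| Primary level | 120 | attends to seek care for these disorders | not eligible on the plain wording |

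No group is defined by having been screened, and none requires an NCD.

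**Effect on the screening mean.** Let q be the share of screened people who are positive, and let μ₊ and μ₋ be the mean spending of positives and negatives. The mean for everyone screened is qμ₊ + (1 − q)μ₋. The sample can supply at most μ₊. The error is therefore

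μ₊ − [qμ₊ + (1 − q)μ₋] = (1 − q)(μ₊ − μ₋).

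The article gives none of q, μ₊ and μ₋, so no figure follows. The error vanishes only if everyone screens positive or if the two groups spend the same. The interviewed positives may also already be paying for management, which would make their screening spending hard to separate.

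**Effect on the management mean.** Let s be the share of interviewed MSUD patients who are NCD patients of the model, and R the ratio of mean spending in the others to mean spending in them. The pooled mean relative to the target mean is s + (1 − s)R. Neither s nor R is in the article. With values assumed only to show the range:

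| s (assumed) | R = 0.5 | R = 2 |
|---|---|---|
| 10% | 0.10 + 0.90 × 0.5 = 0.55 | 0.10 + 0.90 × 2 = 1.90 |
| 50% | 0.50 + 0.50 × 0.5 = 0.75 | 0.50 + 0.50 × 2 = 1.50 |
| 75% | 0.75 + 0.25 × 0.5 = 0.875 | 0.75 + 0.25 × 2 = 1.25 |

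At R = 1 there is no distortion for any s.

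**The case against.** The best defence is that care for these disorders at primary level can be read to include being screened. Table 1 gives sub-centres and Ayushman Arogya Mandirs screening and linkage but no diagnosis or treatment, the intervention package counts screening as a component, and the analysis section treats it as a service accessed. That reading is possible. It still sits badly with a model in which people come for NCD care and are then screened, and if it is intended, one sentence is needed to say so.

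A second defence is study-wide wording. The Recruitment row of Table 6 and the Data governance section both refer to people being screened for, or diagnosed with, an NCD. These are general statements and do not alter the specific exit-interview rule. They do mean that the absence of an NCD requirement is inferred from silence.

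Third, the interview instrument is to record clinical characteristics, which could capture NCD status. That would help the management mean if reporting by NCD status were planned, but it cannot supply respondents who were never recruited. Figure 4, which belongs to this part, is not available. An article may leave eligibility detail to a fuller document, but here it states a rule, and the rule is what does not fit.

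Three stronger readings are tempting and are not supported:

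- A reader might infer that most screened people are negative, because the Introduction cites 9.3–23% comorbid depression (leaving 77–91% without it). That range covers depression alone and is not a screening result; adding anxiety, tobacco and alcohol lowers the unaffected share by an unknown amount.
- A reader might infer that the 220 of 340 interviews (65%) at secondary and tertiary level lie outside screening sites. Table 1 withholds screening only from district hospitals and medical colleges. Community Health Centres do screen, and the article does not say which facility types count as secondary.
- A reader might infer that the management figure is taken from the wrong people. It comes from a mixture of unknown composition, which may include many patients of the model.

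**Conclusion.** The mismatch holds. A separate mean out-of-pocket cost of screening is planned, but on the plain wording of the recruitment rule NCD attenders who screen negative cannot enter the sample, whatever their number. The screening mean would describe a selected subgroup and not those who are screened. The management mean may be diluted by MSUD patients who did not come through the integrated pathway. Whether this happens, and by how much, cannot be established, because the article gives neither the share of such patients nor how their spending differs.

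The conclusion rests on two readings: that seeking care for these disorders does not cover attending for an NCD and being screened, and that the general NCD wording elsewhere does not govern the exit interviews. It concerns a descriptive estimate under a secondary objective and is worth correcting because the correction is cheap.

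**What to change.** Within the planned number of interviews:

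1. In Data Collection, reword primary-level eligibility to include consecutive NCD attenders who were screened for MSUD at that visit, whatever the result. Base the screening mean on them.
2. Record NCD status and entry through the model for every respondent. Report the management mean for NCD patients of the model separately from that for other MSUD patients.
3. If screened attenders will not be recruited, delete screening from the out-of-pocket estimates in the conceptual-framework and Data analysis sections.

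The cost is precision. Fewer primary-level interviews remain for the management mean. The split need not be fixed at any particular value, but if half of the 120 are used for screening, the interval for primary-level management widens by √(120/60) = 1.41, about 41%, with the spread of expenditure unchanged. Separate reporting also makes each management subgroup smaller than the pooled sample. Many screened attenders will have travelled for their NCD visit, so the extra spending due to screening may be close to nil. The instrument should therefore ask for it separately; a near-zero answer would still be informative.

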### Data analysis

The data on the quantity and associated costs of input resources will be recorded in Microsoft Excel. The costs of shared resources, such as human resources, space, equipment, and furniture, will be allocated to specific services using appropriate apportioning methods. The total and per-unit incremental costs incurred, along with their distribution across the various types of inputs and services provided at each facility, will be determined. Additionally, the mean out-of-pocket expenditure per individual will be calculated based on the type of service accessed (screening or management of selected disorders).

### Data governance (Collection, Management, Confidentiality, Security, and Quality Control)

The study will collect both qualitative and quantitative data as a part of a mixed-methods approach to capture primary and facility-level secondary data. The data shall be collected using the direct interviews of health facility-level persons engaged in planning and administration of the health care delivery systems, HCWs, and the persons being screened for or diagnosed with NCDs (quantitative and qualitative) and records available at various healthcare facilities. Data with respect to the screening of MSUDs will occur at multiple levels across the complete continuum of care, including initial screening, diagnosis, treatment, referrals, and follow-ups through a Clinical Decision Support System (CDSS) facilitated through a mobile application. Further, the data related to capacity-building-related activities and outcome measures on the training activities of CDSS will be managed through REDCap [38,39].

Data for implementation outcome measures shall be collected from the health facilities. The details of the same have been provided in Table 8. The data for clinical outcome measures shall be collected from the HCWs and the persons screened for and diagnosed with NCDs. The data for the process outcome measures shall be collected from the health facility level, persons engaged in planning and administration of the health care delivery systems, and HCWs. The nature of data collected from each of the aforementioned shall be based on the outcome measures that have been described in the section on outcome measures.

The mobile application platform will be rolled out in the form of hybrid architecture supported by open-source platforms for both the frontend as well as the backend server-end processing. The frontend of the digital platform will be powered by the cross-platform framework flutter for providing seamless connectivity across various devices. The application backend will be supported by an open-source, high-level Python framework renowned for its scalability, reliability, and rapid development.

In order to accommodate the multiple model refinements inherent in the implementation research project, the software changes will be managed through an agile software development framework with stringent version control for all the software artifacts. The code base changes will be managed through an open-source version control system with the adoption of zero-downtime deployment strategies during the feature rollouts and upgrades. The complete platform will undergo a comprehensive security audit through a CERT-In-empaneled agency for assessing the vulnerabilities at multiple levels. The deployment of the application will be at the Data Centre of the Indian Council of Medical Research (ICMR), Headquarters with the provision of a scalable environment for upscaling the resources on a requirement basis in order to handle varying loads without performance degradation. The data center will facilitate redundant compute and storage components to minimize downtime due to hardware failures and real time data replication along with automated remote backup functionality.

The identity of individual participants will be kept confidential and in adherence to the principle of data minimization, only the bare minimum participant data will be collected through the mobile application, and sensitive data will undergo pseudonymization before being transmitted over the network. The data will be transmitted between mobile application and the server using end-to-end encryption using highly secure protocols like Hypertext Transfer Protocol Secure (HTTPS) and Transport Layer Security (TLS). No data will be stored on the mobile devices, while sensitive data at rest will be stored using 256-bit encryption. The access to data will be strictly through the mobile application controlled through a strict multi-factor authentication (MFA) mechanism along with role-based authorization for ensuring that the users have access to data for which they are authorized.

The access to mobile applications will be monitored through audit logs for any unauthorized access attempts, suspicious actions, or data breaches. All the stakeholders will be trained in capacity-building training for the data security best practices before using the mobile application, and comprehensive data management guidelines will be crafted detailing the procedures for data handling, storage, and accessibility.

The quality control measures that shall be put in place shall include the built-in validation rules, auto-calculation logics, and mandatory field checks, including the study related semantics checks. The respective rules will be appropriately incorporated in the mobile application as well as the REDCap. The data captured through all the sources will undergo regular audits for consistency, missing values, and other study-specific validation rules. Deidentified research data will be made publicly available when the study is completed and published.

### Statistical analysis

#### Quantitative analysis.

Data analysis would be done with IBM SPSS software (Version 25.0) and R software (Version 4.5.1). Nominal or categorical variables would be summarized as frequency and percentage. Continuous variables will be summarized as mean and standard deviation when normally distributed and as median and interquartile range (IQR) when non-normally distributed. We shall assess the percentage of the cases seeking NCD care who shall be offered screening, linkage to care, and management of common mental disorders and substance use disorders following the implementation model. Appropriate statistical analyses will be conducted based on the type of data and study design. Comparisons of mean scores between two independent groups will be performed using the independent samples t-test or the nonparametric equivalent if the assumption of normality is violated. For comparisons involving more than two independent groups, one-way ANOVA will be employed. To assess changes in outcome measures over time within subjects, one-way or two-way repeated measures ANOVA will be used, depending on the number of within- and between-subject factors. For categorical variables, associations between independent groups will be examined using the Chi-square test, while the McNemar test will be applied to assess changes in paired categorical data (e.g., pre- and post-intervention). Comparisons of paired quantitative data, such as baseline and post-intervention measurements within the same group, will be conducted using the paired t-test or its nonparametric alternative, such as the Wilcoxon signed-rank test, depending on data distribution. A two-tailed test will be employed. P < 0.05 will be taken to be the statistical significance level. If clustering of variables is detected during analysis, cluster analysis techniques will be employed to explore these patterns.

